#### Effectiveness evaluation.

The primary endpoint (number of ASE after 12 months) will be analyzed according to the ITT principle. The ITT population of the IG comprises all patients enrolled in the NCM by the end of the nine-month recruitment period, receiving at least 12 months of care. The smallest unit of analysis is the individual patient, as outcomes are assessed at patient level. In a baseline analysis, sociodemographic and clinical characteristics of the IG will be compared with those of the matched CG to assess the effectiveness of the matching procedure and identify potential determinants of the study endpoints [34,35]. The significance of the differences will be tested using linear mixed models for continuous variables with normal distribution, logistic models for binary variables, and the chi-square test and Fisher’s test for categorical variables. Subsequently, the rate of ASE in the IG and CG will be analyzed using multi-level regression models with patients nested within practices to account for the hierarchical structure of the data [36]. As a sensitivity analysis, models with cluster-robust standard errors at the practice level will be estimated. Relevant covariates identified in the initial analyses will be included in adjusted regression models [37].

Continuous secondary endpoints, including healthcare costs, will be analyzed using adjusted mixed linear models. Mortality will be assessed using survival analyses, while binary outcomes will be analyzed using generalized linear mixed models. Covariates will be selected analogously to the primary analysis. Extensive sensitivity analyses are planned to assess the robustness of the evaluation parameters. The choice between matched datasets derived from KVBW or AOK-BW routine data will depend on the respective endpoint as specified in Table 2. Statistical significance will be defined as a two-sided p-value <0.05. Where relevant, 95% confidence intervals are provided.

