### The PRIMA intervention

The PRIMA intervention encompasses different elements at the practice level focusing on the aspects of continuity, comprehensiveness and subsidiarity of care provided by the practices (Fig 2). Core of the intervention is the introduction of PNs with their profession-specific competencies to the existing practice team. Intervention development was guided by the CCM. The PN introduces a NCM offering services beyond regular care currently provided. Within this NCM, the PN is to deliver seven defined tasks in the care for patients with chronic conditions, namely: 1. integration of PN into regular physician-led consultations, 2. conduct of initial and follow-up assessments to support comprehensive evaluation of care in the home setting, 3. coordination of care, 4. participation in interprofessional case conferences, 5. proactive monitoring of the care trajectory, 6. provision of patient education and 7. management of patient inquiries, including acute intervention in crisis. The intervention will be delivered over the full observation period, with a minimum duration of 12 months of follow-up per patient. In order to prepare the intervention, the PNs were employed six months in advance to the start of the intervention in January 2026. Three workshops of each two full days were held before the start of the intervention to prepare the PNs for the NCM. The workshops encompassed information on the PRIMA study and its design, including information and training for the seven tasks to be delivered. Furthermore, the workshop included topics like working in multiprofessional teams, communication skills and the own understanding of the PN role within the practice team. Prior to the start of the intervention, GPs and other team members were invited to participate in two so called “network meetings” providing the participating practice teams as a whole with relevant information regarding the conduct of the study. During the intervention phase, quality circles for the PNs take place on a monthly basis to support intervention delivery. Furthermore, during the first six months of the intervention, another two-day workshop will be held. As the role of the PN with defined tasks beyond regular care is novel to the practice teams, change management support is offered. All PN patient contacts are documented by the PN in a work diary during the intervention phase. Documentation includes baseline data (e.g., age, sex, date of inclusion, presence of inclusion criteria) and reason for contact, type of contact, activities performed, provided healthcare services, time expenditure (minutes), and, where applicable, additional comments in a free-text field. All elements of the intervention are delivered by the project partner IGES in collaboration with KVBW.

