
**Fig 2 pone.0357117.g002:**
[figure not shown]
New care model in PRIMA.

Participating practices are offered the optional use of SmED (Strukturierte medizinische Ersteinschätzung in Deutschland, structured medical initial assessment tool), a structured software tool for medical initial assessment. SmED supports urgency assessment and facilitates allocation of patients to the most appropriate professional within the practice team.

Participants in the PRIMA study may receive any concomitant care as part of routine healthcare within the German statutory healthcare system. The intervention is delivered as part of routine primary care in participating practices and does not interfere with or restrict other aspects of patients’ healthcare utilization.

As the PRIMA intervention is an organizational care model implemented at practice level, adherence is primarily supported through structured training of participating practice teams, and PNs especially, provision of implementation support, and continuous contact with the study coordination team. No specific adherence measures are applicable for comparator patients, as the CG is based on routine data reflecting usual care without active participation requirements.

Participants will remain in the analysis population unless they withdraw consent or data availability ceases. In case of death, participants are retained in the intention-to-treat (ITT) population, and data are included up to the time of death. As the PRIMA intervention is implemented at the practice level as an organizational care model, no individual-level modification of the intervention is foreseen. Practices may discontinue participation in the intervention in case of organizational changes. However, no modifications of the intervention at individual patient level are planned.

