**Secondary outcomes – KVBW data**				
Micro	ASE per person-year	ASE rate adjusted for patient-specific observation time	KVBW	Intervention period
Micro	Patients with ≥1 ASE	Proportion of patients with at least one ASE	KVBW	12 months
Micro	Ambulatory emergencies	All emergency contacts independent of diagnosis	KVBW	12 months
Micro	Ambulatory emergencies per person-year	Rate-adjusted emergency contacts	KVBW	Intervention period
Micro	GP utilization	Number of GP contacts / quarters with GP visits	KVBW	Intervention period
Micro	Specialist utilization	Number of specialist contacts / quarters	KVBW	Intervention period
Meso	Treatment intensity	EBM points per patient and per practice	KVBW	Intervention period
Meso	Continuity of care	Continuity-of-Care Index (e.g., Bice–Boxerman)	KVBW	Intervention period
Meso	Care coordination	Number of providers; referral-based specialist visits	KVBW	Intervention period
Micro	Preventive care	Vaccination rates (influenza, pneumococcal, COVID-19)	KVBW	Intervention period
Macro	Outpatient costs	Cumulative outpatient costs incl. intervention costs	KVBW	12 months
Macro	Outpatient cost-effectiveness	Cost per outcome achieved	KVBW	12 months

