### Safety considerations

No direct medical harms are expected from participation in the PRIMA trial, as the intervention does not involve pharmacological or invasive procedures. Adverse events are not expected to occur in a systematic clinical sense and will therefore not be collected using a structured adverse event reporting system. Potential risks are primarily organizational in nature and may include increased workload or temporary workflow disruptions within participating practices during implementation of the intervention. Participation in the PE is voluntary and not associated with any major risks or burdens. It is possible that participants may feel uncomfortable or burdened during the interviews. If this occurs, they may contact the study leadership. Participants are free to discontinue the interview at any time and to withdraw their consent to participate. If participants find it difficult to answer certain questions in the questionnaires or interviews, these may be skipped. The theoretical risk of data loss cannot be completely ruled out. Any relevant unintended effects reported by participating practices will be documented descriptively and considered in the PE. All identified unintended effects meeting relevance criteria for service delivery will be reported in study publications.

Protocol deviations are primarily relevant at practice level, as the intervention is implemented at cluster (practice) level. Deviations may include partial or delayed implementation of intervention components, such as incomplete integration of the PN. These deviations will be documented descriptively within the PE but will not affect inclusion of practices or patients in the primary effectiveness analyses. At patient level, protocol deviations are not applicable, as outcomes are assessed using routinely collected data independent of patient-level intervention adherence.

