### Missing data

Missing data are expected to be minimal, as outcome data are derived from routinely collected administrative healthcare databases (SHI and KV data). Nevertheless, incomplete follow-up may occur due to changes in insurance status, migration outside the data capture area, or death. Such missingness will primarily result in right-censoring of observation periods. Analyses will account for this using appropriate model-based approaches inherent to survival and mixed-effects regression models, which allow inclusion of all available observations under a missing-at-random assumption conditional on observed covariates. No imputation will be performed for fully missing outcome periods; however, sensitivity analyses will be conducted to assess the robustness of results to potential informative censoring. For the quantitative part of the PE, multiple imputation approaches will be applied if needed.

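### The intervention group's ITT definition contains a 12-months-of-care clause that, read literally, contradicts the article's own rules on deaths and incomplete follow-up

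*Protocol article*

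**What the plan says.** Four places in the protocol article bear on who is analysed for the primary endpoint.

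- **Effectiveness evaluation.** "The primary endpoint (number of ASE after 12 months) will be analyzed according to the ITT principle". The ITT population of the intervention group then "comprises all patients enrolled in the NCM by the end of the nine-month recruitment period, receiving at least 12 months of care". No corresponding sentence defines the control group's population. The same paragraph goes on to say that the rate of ASE is modelled with multilevel regression.
- **The PRIMA intervention.** "Participants will remain in the analysis population unless they withdraw consent or data availability ceases". On deaths it is explicit: "In case of death, participants are retained in the intention-to-treat (ITT) population, and data are included up to the time of death".
- **Missing data.** Insurance changes, moves out of the data area and death are named as causes of incomplete follow-up. "Such missingness will primarily result in right-censoring of observation periods", and the models are to use every available observation.
- **Safety considerations.** Practice-level deviations, such as delayed or partial implementation, "will not affect inclusion of practices or patients in the primary effectiveness analyses".

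On the outcome, the Outcomes section and Table 2 define the primary endpoint as a number of ASE over 12 months. Table 2 also lists a secondary outcome over the whole intervention period, described as "ASE rate adjusted for patient-specific observation time".

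**The concern.** An ITT population is fixed at enrolment. Whether a patient goes on to receive 12 months of care is known only afterwards, and it depends on survival and on staying with the model. A programmer who takes the Effectiveness evaluation sentence at its word would filter on it. The intervention arm would then contain only survivors and completers, and nothing in the article tells the programmer to filter the controls in the same way.

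The patients have life-limiting chronic disease and are unstable or at high risk of decompensation (Table 1). Some deaths within a year are therefore plausible, although patients whom the GP expects to live less than a year are excluded. If patients near death have more emergencies, removing them from one arm lowers that arm's ASE rate without any treatment effect. If the same set were also used for overall survival, no intervention death could be seen in the first 12 months. The article does not say that it will be.

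A linked ambiguity is that the primary endpoint is labelled a number but modelled as a rate, and no exposure term is named. Once deaths are kept, the choice matters, because a count without exposure time reads an early death as fewer emergencies.

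**Working it through.** The article gives no figure for the size of this population effect, so there is none to reproduce. The check has three parts.

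**1. The same patient under each rule**

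| Intervention patient | Effectiveness evaluation, literal | The PRIMA intervention | Missing data |
|---|---|---|---|
| Dies in month 5 | Out | In, data to death | In, censored |
| Stops PRIMA care in month 5, claims continue | Out | In | In, nothing missing |
| Withdraws consent in month 5 | Out | Leaves | Not addressed |
| Data cease in month 5 | Out | Leaves | In, censored |
| Completes 12 months | In | In | In |

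The first two rows are the conflict that matters: one section removes the patient and two keep the patient. Withdrawals leave under either population rule. Patients whose data cease are treated differently by the last two columns, which the fix also settles.

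**2. Calendar**

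Recruitment runs from 1 January to 30 September 2026 (Recruitment), and the data end on 30 September 2027 (Data). Available follow-up is therefore 21 months for the first patient and 12 months for the last. Every enrolled patient can reach 12 months administratively. Read as a condition, the clause therefore removes nobody for late entry. It removes only those who die or leave.

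**3. Illustration of direction and size**

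None of these inputs is in the documents, apart from the 15% target effect (Sample size calculation) used for scale. Assumptions: no true effect; restriction in the intervention arm only; survivors' rate set to 1; 12-month mortality d = 5% or 10%; decedents' ASE rate k = 2 or 3 times that of survivors; decedents at risk for half a year.

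- Person-time rate in unrestricted controls: [(1 − d) + 0.5dk] / [(1 − d) + 0.5d]
- Mean count per unrestricted control: (1 − d) + 0.5dk
- Spurious ratio = 1 divided by either quantity, because the restricted intervention arm has the value 1.

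| d | k | Person-time rate, controls | Ratio | Mean count, controls | Ratio |
|---|---|---|---|---|---|
| 5% | 2 | 1.000/0.975 = 1.026 | 0.975 | 1.000 | 1.00 |
| 5% | 3 | 1.025/0.975 = 1.051 | 0.951 | 1.025 | 0.976 |
| 10% | 2 | 1.000/0.950 = 1.053 | 0.950 | 1.000 | 1.00 |
| 10% | 3 | 1.050/0.950 = 1.105 | 0.905 | 1.050 | 0.952 |

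The range is about 0.90–0.98 on person-time rates and 0.95–1.00 on raw counts; the planned effect corresponds to 0.85. On counts the bias vanishes at k = 2, because half a year at twice the rate gives as many events as a full year at the survivors' rate. If controls were restricted in the same way, the ratio in this illustration would be 1.00 throughout. Widening the inputs to 2–10% mortality and k = 1.5–4 moves the person-time ratio across 0.995–0.864, so the result is driven by the assumptions.

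**The case against.** The strongest reply is that the clause only describes planned follow-up. It comes after a comma, the calendar gives the last enrolled patient 12 months, and The PRIMA intervention uses similar language for the planned duration: "with a minimum duration of 12 months of follow-up per patient". The only sentence that speaks directly about deaths keeps them, Matching describes the analysis population without a completion condition, and Missing data already plans censoring and sensitivity analyses for informative censoring. All of this stands. It makes the benign reading quite possible. It does not remove the problem, because the clause sits in the sentence that defines the population.

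Some stronger readings are tempting and are not supported:

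- **That the trial will drop deaths and dropouts.** The text conflicts with itself; it does not settle the matter in that direction.
- **That up to 28% of patients are at stake** (1 − 0.80 × 0.90, from the dropout allowance in Sample size calculation). That allowance is not broken down by reason, and withdrawals and data loss leave under The PRIMA intervention too. The disputed group is deaths and patients who stop PRIMA care while claims continue; the article gives no number for it.
- **That the bias could reach two thirds of the target effect.** This takes the most extreme cell above, on person-time rates only, with assumed inputs.
- **That exposure time is considered only in the secondary outcomes.** Effectiveness evaluation speaks of a rate for the primary analysis, and Missing data handles censoring. What is missing is agreement between the count label and the rate model.
- **That controls are unrestricted.** The article is silent on this.

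Safety considerations points towards broad inclusion, but it concerns implementation deviations, not deaths or departures.

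**Conclusion.** The contradiction is real and lies in the definition of the primary analysis population. Taken literally, the Effectiveness evaluation sentence conditions ITT membership on a post-enrolment event and excludes patients whom The PRIMA intervention and Missing data keep. Applied that way to the intervention arm only, it would tend to favour the intervention through survivor and completer selection, and the ITT label would not be accurate.

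Confidence is high for the conflict of wording and low for any size. The ratios of 0.90–0.98 (person-time) and 0.95–1.00 (counts) rest on assumed mortality, assumed rates before death, half a year at risk and unrestricted controls. They show the direction under those inputs and are not an estimate for this trial. Whether the exclusion is intended cannot be decided from the article.

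**What to change.** 1. Delete the 12-months-of-care clause from the ITT definition, or move it to the description of planned follow-up.
2. Define the ITT population as all patients enrolled by 30 September 2026. Give each matched control an index date and follow both arms under the same rule, to the earliest of 12 months, death or end of data.
3. State that the primary ASE rate model uses log person-time as an offset, and align the wording of the endpoint in Outcomes and Table 2 with it. Report mortality by arm beside the primary result.
4. Keep 12-month completers only as a sensitivity analysis, applied to both arms.

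The cost is a few sentences, recorded as an amendment. Dates of death and end of data have to be available for both arms, which the planned censoring already requires. AOK BW does its own matching before delivery, so it needs the same index-date rule in advance. Analysis begins in October 2027 (Study timeline), so the change can be made before any outcome is analysed.

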### Sample size calculation

For the sample size and power calculation, a baseline rate of 0.20 ASE per patient per year is assumed. In the general population, ASE rates range between 4% and 8% [22]. As the study population consists of patients with chronic conditions selected based on clinical judgement and expected to benefit from enhanced care, a higher baseline rate is expected. Based on published evidence suggesting a 20–40% reduction in ASEs through improved ambulatory care [23], a conservative effect size of 15% is applied.

The study follows a parallel cluster design with 20 practices per arm and approximately 112 patients per practice. This accounts for an anticipated dropout of 20% at practice level and 10% at patient level. The design includes 12 months of pre- and 12 months of post-intervention observation [24]. An intra-cluster correlation coefficient (ICC) of 0.01 is used. Under these assumptions and a two-sided alpha of 5%, the study achieves a statistical power of 82% to detect a 15% reduction in ASE rates.

The PE within PRIMA does not assess a primary endpoint of the study. Therefore, no separate sample size calculation was required for the PE. Instead, the sample size of the PE is determined by the total population of all participant groups included in the PRIMA study and by the methodological approach chosen within the PE sub-projects. For the questionnaire-based quantitative PE, all patients included in the main study as well as all staff members of the participating practices will be included (estimated n = 2,000). To ensure sufficient thematic breadth regarding the research questions – while simultaneously aiming for thematic saturation – a total of 4 practices will be included in the qualitative case studies, leading to about 60 individual interviews (30–60 minutes) with patients, relatives, and practice staff, along with approximately 16 qualitative activity logs. In addition, 4–5 cross-site focus groups (approximately 120 minutes each) with members of the PRIMA teams and stakeholders at interface levels (e.g., care support centers) are planned.

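### The intervention group's ITT definition carries a clause on 12 months of care that, as written, is a post-enrolment condition and conflicts with the protocol's own rules on death and incomplete follow-up

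*Protocol article*

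**What the plan says.** The Effectiveness evaluation section names the number of ASE after 12 months as the primary endpoint, analysed by intention to treat. It says that the intervention group's ITT population "comprises all patients enrolled in the NCM by the end of the nine-month recruitment period, receiving at least 12 months of care". No corresponding sentence is given for the matched controls.

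Other sections also bear on who is analysed:

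- The PRIMA intervention (text after Fig 2), on death: "In case of death, participants are retained in the intention-to-treat (ITT) population, and data are included up to the time of death".
- Same place, on leavers: "Participants will remain in the analysis population unless they withdraw consent or data availability ceases".
- Same place, on practices: "Practices may discontinue participation in the intervention in case of organizational changes". The analysis status of their patients is not stated there.
- Missing data, on insurance change, migration and death: "Such missingness will primarily result in right-censoring of observation periods".
- The PRIMA intervention, earlier in the section, describes delivery of the model "with a minimum duration of 12 months of follow-up per patient".

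**The concern.** An ITT set should be fixed by what is known at enrolment. Receipt of 12 months of care is an outcome of follow-up: a patient who dies or moves away in month 5 does not have it. A patient whose practice stops delivering the model may not have it either, depending on what care is taken to mean. Read literally, the sentence attaches the ITT label to a completer set.

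Two analysts working from this article could build different primary populations, one following the Effectiveness evaluation section and the other the text after Fig 2. If the literal version were used and controls were not restricted in the same way, every intervention patient would have survived 12 months by construction while controls would not. Those removed could well be the sicker patients, since Table 1 selects people who are unstable or at high risk of decompensation. The ASE rate, the costs and overall survival would then be compared between a selected and an unselected group.

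**Working it through.** **1. The rules applied to the same patients**

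| Patient in the intervention group | Effectiveness evaluation, read literally | Other sections |
|---|---|---|
| Dies in month 5 | Out: 12 months of care not received | In, with data up to death (text after Fig 2); censored (Missing data) |
| Moves away or changes insurer in month 5 | Out | Censored, with available observations used (Missing data) |
| Practice stops in month 5, patient still in the claims data | Out if care means the new model; in if it means any care | No explicit rule |

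The first row is a direct contradiction. The second is a mismatch. The third is left open.

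**2. The calendar reading**

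Recruitment closes on 30 September 2026 (Recruitment). The data run to 30 September 2027 (Data). The difference is exactly 12 months, so the last patient enrolled can be followed for 12 months. The clause is therefore compatible with a plain description of available follow-up. However, it speaks of care received, not of observation time available.

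**3. Possible size under the literal reading**

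No figure in the article depends on this clause, so there is none to reproduce. From Sample size calculation: control rate 0.20 ASE per patient-year and a 15% reduction, so the target rate is 0.20 × 0.85 = 0.17 and the target rate ratio is 0.85.

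Assumed inputs, not in the document: a fraction d of intervention patients is excluded; they have k times the ASE rate of the others; they would have contributed half a year each. Controls have the same mix but are not restricted. There is no true effect.

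With person-time in the model:

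RR = (1 − 0.5d) / (1 − d + 0.5dk)

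- d = 0.03, k = 2: 0.985 / 1.000 = 0.985
- d = 0.03, k = 3: 0.985 / 1.015 = 0.970
- d = 0.10, k = 2: 0.950 / 1.000 = 0.950
- d = 0.10, k = 3: 0.950 / 1.050 = 0.905
- k = 1, any d: 1.00, no bias

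Against the 15% target, the spurious reductions of 1.5% to 9.5% are between one tenth (1.5/15) and just under two thirds (9.5/15) of the effect sought.

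If counts are analysed without a person-time offset:

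RR = 1 / (1 − d + 0.5dk)

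- d = 0.10, k = 1: 1 / 0.950 = 1.05
- d = 0.10, k = 2: 1 / 1.000 = 1.00
- d = 0.10, k = 3: 1 / 1.050 = 0.95

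So the direction depends on the excluded patients' rate and on how exposure enters the model.

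**The case against.** The strongest reply is that the clause is only loose wording. The sentence itself begins with all enrolled patients, the Matching section also describes the analysis population by enrolment, the rule on deaths is explicit, and the dates fit a calendar reading. This stands to a large extent. A reader might infer that deaths, leavers and patients of stopping practices are deleted from the intervention arm. The document does not establish that, because other sections say deaths are kept and incomplete follow-up is censored. What the reply does not remove is the conflict between two statements about the same primary population.

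The second reply is that a one-arm restriction is not shown. This also stands: the control-side rule is simply not stated, and a 12-month rule from a matched index date could be applied to controls.

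Three further inferences are tempting but go too far:

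- **Size of the loss.** The "anticipated dropout of 20% at practice level and 10% at patient level" gives 1 − 0.80 × 0.90 = 28%, or about 627 of 20 × 112 = 2,240 patients. These figures are a sample-size allowance. They are not defined as exclusions from analysis, and the article does not say whether 112 is before or after dropout.
- **Survival.** With follow-up spread evenly over 12 to 21 months, removing first-year deaths from one arm gives a death-rate ratio of about 0.375/1.375 = 0.27. That is mean time after month 12 over mean total time in years. It restates the literal reading and is not evidence for it.
- **Supporting contradictions.** The statement that deviations "will not affect inclusion of practices or patients in the primary effectiveness analyses" concerns partial or delayed implementation, not practices that stop. The rule on data availability can be read as ending observation, which agrees with the Missing data section.

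**Conclusion.** The point holds as a contradiction in how the primary population is defined. Read as written, the Effectiveness evaluation sentence conditions the intervention group's ITT set on something that happens after enrolment. That contradicts the retention of deaths and does not fit the censoring rule. The article does not show that anyone will in fact be excluded, or that controls will be treated differently.

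The size is conditional. Under the literal reading, with no mirrored rule in controls and the assumed inputs above, the spurious ASE rate ratio runs from about 0.985 to 0.905 against a target of 0.85. It is 1.00 if the excluded patients have the same rate, and it can exceed 1 without a person-time offset. A bias in the upper part of that range would matter in a non-randomised comparison powered for a 15% reduction. Because the sentence decides who enters the primary analysis, it should be corrected even though the calendar reading may be what was meant.

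**What to change.** 1. In Effectiveness evaluation, delete the closing clause on 12 months of care. Define the intervention ITT set as all patients enrolled with consent by 30 September 2026, regardless of how long care was received or whether the practice continued.
2. State that observed person-time counts from the index date to death, loss of data or month 12, whichever comes first, and that matched controls have the same index-date and censoring rule.
3. In the text after Fig 2, state that loss of data ends follow-up and does not remove the patient, and that data collected before withdrawal are kept where consent allows.
4. Label any analysis limited to patients with 12 months of care as a sensitivity analysis.

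If the clause was meant only as a calendar statement, these changes record that intention. The cost is about one sentence in each of the two sections, plus matching text in the analysis plan. No new data are needed. The Study timeline has recruitment running to September 2026 and analysis starting in October 2027, so the change can be made and documented before outcomes are analysed.
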